### Methods in analysis to handle protocol non-adherence and any statistical methods to handle missing data

Data will be analyzed on an intention-to-treat basis to include all participants based on the random allocation regardless of whether the intervention has been received or not. Adherence to intervention or withdrawal, which is recorded by our trained research assistants on a weekly basis, serves as a covariate and will be included in the data analysis.

Missing data will not be imputed for main primary and secondary analyses. As sensitivity analyses, these analyses will be repeated, using multiple imputation with chained equations for missing data.

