## Methods

### Trial design

The protocol complies with a randomized controlled equivalence trial, double-blinded, parallel (1:1 ratio), and exploratory approved by the Research Ethics Committee of the Hospital de Clínicas of the Universidade Federal do Parana (CAAE: 01,378,118.7.0000.0096). The individuals are allocated through simple randomization into two groups. All items in the Data Set of the Register of Tests by the WHO were recorded on the database of the Brazilian Clinical Trial Registry (RBR – 5qs9k2n). Any alteration in the protocol is informed to the above-mentioned bodies. When preparing this protocol, we used the SPIRIT reporting guidelines [17], and a table with the standard protocol items (SPIRIT) is presented in Table 1. The SPIRIT checklist is available as an additional file (Additional file 1).

**Table 1 Tab1:** Time schedule of enrollment, interventions, assessments, and visits for participants according to Recommendations for Interventional Trials (SPIRIT)

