**Fig. 2 Fig2:**
[figure not shown]
Schematic drawing of experimental design. T0 to T5 represents the assessment stages. DD, dorsal decubitus; EG, experimental group; MHM, mechanical hyperinflation maneuver; CG, control group

Assessments will range five stages: T0 (monitoring start), T1 (before ventilation maneuver for the intervention or control groups), T2 (end of ventilation maneuver our control), T3 (after tracheal aspiration), and T4/T5 (monitoring after 10 and 20 min of procedure). The five initial minutes are required for the initial collection of hemodynamic, ventilation, and neurological data. After the start of this period is T1 with a 10-min duration, followed by T2 and T3, with a 5-min duration each. The individuals in T1 who constituted the MHM group will have their ventilation parameters altered for 10 min according to the lung hyperinflation maneuver adopted, subsequently returning to the baseline values. During this period, the individuals in the control group will be only monitored. In T2, both groups will be subjected to tracheal aspiration; subsequently, data will be monitored for 5 min. Finally, the individuals of both groups were monitored at T4 and T5, 10 and 20 min after the procedure, respectively, to verify vital data stabilization (Fig. 2).

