### Experimental group

We will perform ventilation adjustments to proceed with the MHM. The patient will be maintained on dorsal decubitus at the bedside at 30°, on assisted ventilation mode, and controlled volume. Vt will be increased by 150% based on ideal tidal volume; square wave V; inspiratory time (Ti) equal to 1.5 s, adjusted to a peak of inspiratory flow (PIF) lower than the peak of expiratory flow (PEF); RR of 14 irpm, reduced in case of auto-PEEP; PEEP 8 cmH_2_O; FIO_2_ minimum of SpO_2_ of at least 94%. These parameters will be preserved for 10 min. The MV alarms will be adjusted to allow the safety of the maneuver; in addition, in case of Ppeak above 40 cmH_2_O or plateau pressure (Pplateau) above 30 cmH_2_O, the maneuver is immediately interrupted and the previous parameters reestablished. The hyperinflation maneuver will not be associated with any other bronchial hygiene maneuver.

After 10 min, the recommendations of the American Association for Respiratory Care [21] (2010) will be applied in the aspiration procedure, suggesting that the patients are ventilated with FIO_2_ at 100% for 30 s before and 60 s after the procedure to avoid hypoxemia. In this study, each patient will be subjected to tracheal aspiration for 15 s for three consecutive times through a closed aspiration system with catheter number 14. Subsequently, the ventilation parameters will be readjusted according to the initial parameters.

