### Sample size

During an extensive literature search, no randomized clinical trials were found that investigated the effect of MHM on CHF in post stroke patients. Thus, it was decided to use a study that investigated the effects of a physiotherapy technique on ICP for the sample calculation.

To obtain the sample size needed for this study, we used the combination of statistical software’s R and G-Power 3.1. First, we extracted the intracranial pressure with the techniques performed in the study bellow [28]. From this previous work, we detected that the median value of ICP for the control group was 16.9, and for the intervention group, it is 11.7. Then, we calculated the Cohen-D effect size from the medians using the package ‘rcompanion’ in R [29]. The final step using the GPower is where we estimate with a power of 95% and a confidence level of 95% the minimum sample size for a *T-Student* equivalence test [30]. The total number of subjects is 60, equally distributed in two groups of 30 patients.

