### Statistical methods

The collected data will be organized on a spreadsheet and summarized using techniques of descriptive statistical analysis. The qualitative variables will be summarized by building frequency tables and the quantitative variables by calculating the descriptive measures (average, mean, standard deviation, and percentiles 25–75).

The evaluations’ primary outcome and secondary outcomes will be made in 5 different times; for that, the data will be analyzed by analysis of variance (ANOVA) two-way for repeated measures with the Tukey post-test for results that present normal distribution and homogeneity of variances, verified by the test of Shapiro–Wilk and Average in Levene, respectively.

We will be using the statistical software Statistical Package for the Social Sciences (SPSS) (IBM—version 22) to analyze the collected data. Our research hypotheses will be tested using non-parametric methods. Wilcoxon test with Kruskal–Wallis post-test will also be applied (intergroups). The level of significance established was *p* ≤ 0.05. The evaluation of results and data analysis will be carried out by an independent professional.

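### In this equivalence trial intention-to-treat is the only analysis basis named, and receipt of the single 10-minute maneuver enters only as an uncoded post-randomisation covariate recorded weekly

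*Protocol article*

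**What the plan says.** All references are to the protocol article.

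- **Trial design** calls the study a "randomized controlled equivalence trial, double-blinded, parallel (1:1 ratio), and exploratory" trial.
- **Interventions** (text under Fig. 2) and **Experimental group** set the exposure: patients in the maneuver arm "will have their ventilation parameters altered for 10 min", once. **Primary outcome** names T2, the assessment just after the maneuver, as the key time point.
- **Experimental group** provides for early stopping. If airway pressure limits are exceeded, "the maneuver is immediately interrupted and the previous parameters reestablished". **Safety assessment and adverse effects** adds vital-sign criteria for interruption, and suspends data collection on instability or excessive airway pressure.
- **Methods in analysis to handle protocol non-adherence** (and missing data) fixes intention-to-treat, "regardless of whether the intervention has been received or not". The next sentence says that adherence or withdrawal, "which is recorded by our trained research assistants on a weekly basis", will be a covariate in the analysis. Missing data are not imputed in the main analyses, and multiple imputation is the only sensitivity analysis named.
- **Statistical methods** gives a two-way repeated-measures ANOVA and non-parametric tests. No covariate appears there.

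**The concern.** Intention-to-treat is cautious when the aim is to show a difference, because undelivered treatment shrinks the contrast and works against the claim. In an equivalence trial the same shrinkage works for the claim. The Discussion hopes to show that hyperinflation can be performed safely in these patients, which is a statement about the maneuver when it is given. A patient whose maneuver was stopped early says little about ten minutes of it, yet counts fully in the experimental arm.

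The plan does take some account of receipt, through the adherence covariate. That device does not repair the problem. Weekly recording looks carried over from a multi-week programme. The variable arises after randomisation. Receipt of the maneuver can vary only in the arm that is meant to get it. No coding is stated, and the described model has no place for it. Depending on the coding, the adjusted group effect answers quite different questions.

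**Working it through.** **1. Time scale.** From the text under Fig. 2: 5 min initial collection + 10 min maneuver + 5 min + 5 min + 20 min follow-up = about 45 min. Adherence is recorded weekly. A weekly entry has no natural meaning for one 10-minute exposure in a 45-minute session.

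**2. The plan's own figure.** Sample size reports 60 patients (30 per arm) for an equivalence t-test at 95% power and 95% confidence. The inputs given are that "the median value of ICP for the control group was 16.9, and for the intervention group, it is 11.7", a difference of 5.2. The SD, Cohen's d and margin are not stated, so 60 can be neither confirmed nor refuted. For two one-sided tests (TOST) at 5% each and a true difference of 0,

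n per arm = 2·[SD·(z0.95 + z0.975)/margin]².

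Solving for n = 30: margin/SD = (1.645 + 1.960)·√(2/30) = 0.93. If 5.2 served as the margin, the SD would be 5.2/0.931 = 5.59. For assumed SDs of 4, 5, 5.5, 6, 7 and 8, n per arm is 16, 25, 30, 35, 48 and 62. The 0.93 SD is used below only as a working margin.

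**3. Route A: maneuver stopped, T2 obtained.** Let a fraction q of the experimental arm receive essentially no maneuver and show no effect, and let δ be the effect in the others. The expected intention-to-treat difference is (1 − q)·δ, so it shrinks by the fraction q.

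To see what this does to the decision, take δ equal to the working margin, so that equivalence of the delivered maneuver should be declared about 5% of the time. Simulation with 30 per arm, SD 1, TOST at 5% per side, 100,000 runs:

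| q (patients of 30) | Expected difference, SD | Equivalence declared, intention-to-treat | Equivalence declared, delivered vs control |
|---|---|---|---|
| 0 | 0.93 | 5.1% | 5.1% |
| 10% (3) | 0.84 | 9.4% | 5.1% |
| 20% (6) | 0.74 | 16.0% | 4.9% |
| 30% (9) | 0.65 | 25.5% | 4.9% |
| 50% (15) | 0.47 | 51.9% | 5.0% |

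The last column holds only because non-delivery was simulated as unrelated to outcome.

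**4. Route B: collection suspended, T2 missing.** Without imputation the patient leaves the T2 comparison. If a fraction q is lost in this way, with mean effect δ₁ against δ₀ in those kept, the observed effect is δ₀ while the effect over all would be q·δ₁ + (1 − q)·δ₀. The shortfall is q·(δ₁ − δ₀). It favours equivalence if those suspended reacted more strongly. The documents give no basis for a number.

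**5. The covariate.** Group and receipt define three cells: control, maneuver delivered, maneuver not delivered. Under the same assumptions as step 3 (4,000 runs each):

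- Coded as *received allocated care* (all controls 1): the group coefficient is delivered maneuver minus control. Equivalence is declared in about 5% of runs at every q, but this is a completer comparison and no longer intention-to-treat.
- Coded as *received the maneuver* (all controls 0): the group coefficient is undelivered maneuver minus control. Its expected value is 0 whatever the maneuver does. Equivalence is declared in 1.5%, 31%, 55% and 79% of runs at q = 10%, 20%, 30% and 50%.

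The article does not say which coding applies.

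**The case against.** **Receipt is not ignored.** A reader might infer that the plan disregards whether the maneuver was given. It does not: the sentence that sets weekly recording also puts adherence into the analysis. This stands, and the point is confined to the covariate being undefined and unsuitable.

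**Stopped patients may well be identifiable.** A reader might also infer that weekly recording makes it impossible to separate interrupted from complete maneuvers later. The documents do not support that. Vital signs are monitored continuously with a physiotherapist present, compliance values are averaged minute by minute, ventilator settings and pressures are recorded, and data go on a paper form. The information is probably at the bedside; the adherence text simply does not ask for it per session.

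**Dilution is not certain.** If collection is suspended, T2 may never be taken, and the patient then cannot dilute the comparison. This also stands. It moves the problem from route A to route B, which can favour equivalence too.

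**No rate is given.** The protocol sets safety limits and predicts no frequency, and the exclusion criteria already remove some patients likely to be stopped. A patient stopped at minute 9 has had most of the exposure, and one stopped for a reaction may show an effect. Hence the percentages are illustrations, not estimates.

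**A completer set may sit in an unseen analysis plan.** That is possible, and its absence from an article is not the point. The point is what the article positively fixes: one analysis basis, weekly recording and an adherence covariate. A fuller plan would have to be reconciled with all three.

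**Intention-to-treat answers a legitimate question**, namely the effect of a policy of attempting the maneuver. That is why it should stay. It is not sufficient alone for a claim about the maneuver as performed.

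**Conclusion.** The point holds in limited form. For a trial labelled equivalence, intention-to-treat is the sole analysis basis named. Receipt of a one-session, 10-minute maneuver enters only through a weekly, uncoded, post-randomisation covariate that the described ANOVA does not contain. Interrupted maneuvers are provided for by the protocol itself, and both of their routes through the analysis can favour equivalence.

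The size cannot be fixed from the documents, because neither a stopping rate nor a margin is given. The shrinkage by q assumes essentially no exposure and no effect in the stopped patients. The rise in falsely declared equivalence from 5.1% to 16.0% at q = 20% further assumes a 0.93 SD margin and a true effect equal to it. Under route A the direction does not depend on those values; under route B it depends on suspended patients having reacted more strongly. Nothing here judges the clinical criteria for interruption.

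**What to change.** 1. Replace the weekly adherence entry with one entry per patient at the session: minutes of hyperinflation delivered, reason for stopping, and whether T2 was obtained.
2. Keep intention-to-treat.
3. Add a prespecified analysis of patients who completed the maneuver against controls, and claim equivalence only if both analyses agree. Both must use the same stated margin, which the article does not give.
4. Report patients without T2 by arm and reason.
5. Remove the adherence covariate from the primary comparison.

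The cost is an added entry on the case form and one further analysis. The second analysis has slightly fewer patients, and completers may be those who tolerated the maneuver best, so it cannot replace intention-to-treat. Requiring agreement makes the equivalence claim slightly harder to reach.

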### Control group

The CG will be positioned in dorsal decubitus at 30° and will undergo initial ventilatory adjustments and tracheal aspiration, the same procedures performed in the EG 2 h before the start of data collection. Between T1 and T2, they will only be monitored, not going through the MHM. In T3, they will be aspirated as well as EG. They will undergo non-invasive ICC monitoring at the same moments as the EG.

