### Safety assessment and adverse effects

The vital signs (heart rate (HR), RR, MAP, and SpO_2_) will be assessed continuously and registered during the assessment stages through a multiparameter monitor Mindray iMEC12, while capnography will be assessed through a monitor and sensor Dräger Vamos®. Criteria for interrupting the intervention are HR < 60 bpm, systolic blood pressure > 180 mmHg, and diastolic blood pressure < 50 mmHg. The ICP assessed in a non-invasive manner will also be monitored during all procedures and 20 min after the end of the collections. The MV alarms will be adjusted to allow to control the airway pressures.

An expert physiotherapist will be present throughout the collection, and in case of hemodynamic and/or neurological instability, as well as an increase in airway pressures above the allowed values, the collection will be suspended, and a physician of the ICU staff will join the procedure.

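### Adherence or withdrawal, observed after randomisation, is made a covariate in an analysis declared as intention-to-treat; used in the main comparison, it can shift the arm effect away from harm

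*Protocol article*

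**What the plan says.** The section on non-adherence and missing data promises analysis of everyone by random allocation, "regardless of whether the intervention has been received or not". The next sentence concerns "Adherence to intervention or withdrawal, which is recorded by our trained research assistants on a weekly basis" and states that this information "serves as a covariate and will be included in the data analysis". Nothing confines it to a secondary or sensitivity analysis, although the same section does use the sensitivity label for multiple imputation.

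Other sections show what produces non-adherence:

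- Experimental group: if peak or plateau pressure passes its limit, "the maneuver is immediately interrupted and the previous parameters reestablished".
- Safety assessment and adverse effects: "Criteria for interrupting the intervention are HR < 60 bpm, systolic blood pressure > 180 mmHg, and diastolic blood pressure < 50 mmHg". Also, "in case of hemodynamic and/or neurological instability, as well as an increase in airway pressures above the allowed values, the collection will be suspended".
- Control group: "Between T1 and T2, they will only be monitored, not going through the MHM".

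The Intracranial compliance section names T2, directly after the maneuver, as the key time for the primary outcome. Trial design calls the study an exploratory equivalence trial. Statistical methods names a two-way repeated-measures ANOVA and rank tests, and mentions no covariate.

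**The concern.** The two adjacent sentences cannot both govern the main analysis. One ignores whether the intervention was received; the other conditions on it.

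This matters more than usual here. Whether the maneuver is completed depends on how the patient responds to it, and up to T2 only the experimental arm has a maneuver that can be cut short. A model with arm and adherence gives interrupted experimental patients a term of their own. What is left in the arm coefficient is mainly a comparison of patients who tolerated the maneuver with controls. The patients most likely to show harm are taken out of the contrast, in a trial whose stated expectation is that the maneuver is safe and leaves intracranial compliance unchanged.

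**Working it through.** **The plan's own figures.** The plan gives no number on this point. Its one computed figure, 60 patients, does not bear on the contradiction. It also cannot be reproduced, because no SD, Cohen's d or equivalence margin is stated. I use it only to obtain an illustrative margin. Two one-sided tests at 5% each, 95% power and 30 per arm imply (1.645 + 1.960) × √(2/30) = 0.93 SD.

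**What the arm coefficient estimates.** Take outcome = a + b·arm + c·adherence, with every control coded adherent. This is an assumption, since the protocol gives neither the model nor the coding. There are then three cells:

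- controls: a + c
- experimental, completed: a + b + c
- experimental, interrupted: a + b

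So b is the mean of the experimental completers minus the mean of all controls.

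**Size with uniform or no harm.** Let a fraction q of experimental patients be interrupted, namely those highest on a standard normal trigger that correlates r with the outcome. The outcome is in SD units and higher is worse. The completers' mean is then shifted by −r·φ(z)/(1 − q), where z is the upper-q normal point.

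- q = 20%: −r × 0.280/0.80 = −0.35r
- q = 10%: −r × 0.1755/0.90 = −0.195r

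| r | shift, q = 10% | shift, q = 20% | true +0.50 SD is estimated as (10% / 20%) |
|---|---|---|---|
| 0 | 0 | 0 | 0.50 / 0.50 |
| 0.3 | −0.06 | −0.11 | 0.44 / 0.40 |
| 0.5 | −0.10 | −0.18 | 0.40 / 0.33 |
| 1 (worst case) | −0.195 | −0.35 | 0.31 / 0.15 |

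Neither q nor r is in the documents.

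**Size with concentrated harm.** If all the harm falls on interrupted patients, completers carry none of it, so b loses the whole average effect as well as the shift above.

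**Simulation check.** There were 30 per arm and 3,000 runs per scenario, with q from 10% to 30%, r of 0, 0.3 and 0.5, margin 0.93 SD and a 90% interval.

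| Scenario | Estimate without / with covariate (SD) | Equivalence declared without / with |
|---|---|---|
| No effect | about 0 / −0.25 to 0 | 93–95% / 79–94% |
| Mean harm 0.50, concentrated | 0.50 to 0.52 / −0.24 to +0.01 | 29–41% / 79–93% |
| Mean harm 0.93, uniform | 0.92 to 0.94 / 0.68 to 0.93 | 4–6% / 5–23% |
| Mean harm 0.93, concentrated | 0.93 to 0.98 / −0.25 to +0.01 | 6–7% / 79–93% |

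In the last two rows true harm equals the margin, so declaring equivalence is an error with a nominal rate of 5%.

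**Weekly recording.** Adding the stage durations in the Interventions section gives 5 + 10 + 5 + 5 + 20 = 45 minutes from start of monitoring to T5. A weekly adherence record has no place in one such session.

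**The case against.** The best defence is that the bias may be small and its route uncertain. Most of that stands as a limit on size.

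- **Triggers.** The named triggers are airway pressure, heart rate and blood pressure, not the P2/P1 ratio or time to peak. Only the undefined neurological instability comes near the outcome. The exclusion criteria (high peak pressure, acute respiratory distress syndrome, pneumothorax, haemodynamic instability) should also lower the interruption rate. So r may be well below 1 and q may be small.
- **Controls.** A reader might infer that controls have nothing comparable to fail. That goes too far. They also undergo tracheal aspiration, the suspension rule is not limited to one arm, and withdrawal can occur in either. A pure completers-versus-all-controls contrast follows only if every control is coded adherent, which the protocol does not say.
- **Model.** No analysis in Statistical methods carries a covariate, and the weekly recording suggests text carried over from another design. It may be a drafting fault. Even so, the sentence stands unqualified, and an analyst who follows it would be following the protocol.
- **Direction.** A reader might infer that the bias runs toward no change. It is a downward shift, not attenuation: with no true effect the estimate moves away from zero, and equivalence becomes somewhat harder to show.
- **Exploratory label.** The label lowers the stakes, but the trial still aims at an equivalence conclusion on safety.

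**Conclusion.** The text is wrong as written. Conditioning on adherence or withdrawal contradicts the intention-to-treat statement beside it; this needs no calculation and no assumption about rates.

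If the covariate is used in the main comparison, the arm effect stops estimating the randomised contrast and tends to move away from harm. That tendency assumes that interrupted patients are, on average, those with worse outcomes. Under the stated coding, with uniform or no harm, the shift is −0.35r SD at 20% interrupted and −0.195r SD at 10%. It is zero when the trigger is unrelated to the outcome. It is larger, up to losing the entire average harm, when harm is confined to interrupted patients.

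Two stronger readings are not supported. One is that a shift of 0.35 SD should be expected: that is r = 1, with interruption decided on the outcome itself. The other is that the randomised comparison is removed outright: the covariate's model and coding are unspecified, and in some scenarios there is no bias. The false-equivalence rates of 79–93% under harm of 0.93 SD likewise rest on fully concentrated harm and a margin back-solved from the sample size.

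**What to change.** - Delete adherence and withdrawal as covariates from the primary and secondary models. Analyse by allocation, keep interrupted patients in their arm, and use their T2 data wherever these were recorded.
- Report interruptions, suspensions and missing T2 values by arm with reasons. Deleting the sentence is not enough: suspended patients may have no T2 value, and the main analysis does not impute, so selection of completers could return through missing data.
- Address adherence in a clearly labelled supplementary analysis, for example a per-protocol result beside the intention-to-treat one. With all controls counted as adherent, a per-protocol comparison has the same arm contrast as the covariate model, so it must not replace the main result. A complier-average analysis is another option.
- Remove the reference to weekly recording, or describe recording within the session.

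The cost is one sentence removed, one table and one supplementary analysis. The sample size and the clinical criteria for interruption are untouched.

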In scenarios of normality of ICP and ICC, there is a proportion between the peaks, where P1 > P2. However, in situations of abnormality, there is a change in the morphology of the ICP waveform, with an increase in ICP associated with a low ICC, with P2 > P1. For the TPP variable, the higher the value found, the greater the chance of the peak being P2, which also corresponds to a decrease in the ICC [22, 23].

In this study, the evaluations will be carried out in five (T1–T5) moments:T0: start monitoring, the interval between T0 and T1 is intended to ensure patient stabilization for the start of data collection;T1: capture initial patient data;T2: assess whether the MHM protocol had effects on ICC;T3: verify whether aspiration combined with MHM could lead to different effects on outcomes;T4 and T5: check whether there was stabilization of parameters related to ICC and respiratory mechanics.

The moment of evaluation T2 is the most relevant for the primary outcome; as for the secondary outcomes, evaluations from T2 to T5 are the most relevant.

Data will be collected through a monitor and analyzed using the Brain4care Analytics System, considering that at a time interval, the software selects an average of pulses to form the waves.

To capture the data, the ICP assessment sensor will be chosen according to the cranial circumference (S, M, L, XL) considering as protocol the lowest sensor possible with reading, following the manufacturer’s recommendations. Data collection will start after the coupling procedure and confirmation by the assessor of reading compatible with the acceptable ICP curves.

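### The only missing-data check assumes missing at random, although T2 readings may be lost because of a bad response, mainly in the experimental arm

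*Protocol article*

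**What the plan says.** The section on non-adherence and missing data sets the main rule: "Missing data will not be imputed for main primary and secondary analyses". Its one sensitivity analysis is that "these analyses will be repeated, using multiple imputation with chained equations for missing data". It also adopts intention to treat and says that adherence or withdrawal "serves as a covariate and will be included in the data analysis". No scenario lets patients with missing readings do worse than those observed.

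Two other sections determine how readings can go missing. *Safety assessment and adverse effects* says that "in case of hemodynamic and/or neurological instability, as well as an increase in airway pressures above the allowed values, the collection will be suspended", and gives vital-sign limits: "Criteria for interrupting the intervention are HR < 60 bpm, systolic blood pressure > 180 mmHg, and diastolic blood pressure < 50 mmHg". *Experimental group* sets limits on peak and plateau airway pressure during the maneuver; if either is exceeded, "the maneuver is immediately interrupted and the previous parameters reestablished".

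On timing, the primary-outcome section states that "The moment of evaluation T2 is the most relevant for the primary outcome". The abstract places T2 after the maneuver and before aspiration. *Control group* says that controls are only monitored between T1 and T2.

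**The concern.** A check on missing data should test the assumption on which the main analysis depends. Here both the main analysis and the check need the unobserved T2 values to resemble observed ones, given what has been recorded. The trial's own rules suspend collection when a patient becomes unstable, which is a situation where that resemblance is doubtful.

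The loss would also tend to be one-sided. Up to T2 the arms differ only in the maneuver, and the limits for interrupting the maneuver can be reached only by patients who receive it.

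The stake is the trial's main conclusion. This is an equivalence trial whose abstract expects no change in intracranial compliance. If patients who tolerate the maneuver badly lack T2 readings, the remaining data look more like no difference. Imputation from those remaining data then appears to confirm the result.

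**Working it through.** The plan has no figure of its own on this point, so there is nothing to reproduce. The check asks what the two stated analyses estimate when T2 is lost through harm.

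**Inputs from the article.** 30 patients per arm (*Sample size*); T2 as the key time; no imputation in the main analyses; chained-equation imputation as the only check.

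**Assumptions, because the article gives no values.** Share of the experimental arm suspended before T2, *p* = 10% to 20% (3 to 6 of 30). Excess of their T2 value over that of tolerant patients, Δ = 1 to 2 SD, upward because the primary-outcome section ties a higher P2/P1 to lower compliance. Suspended patients have no T2 reading, and no controls are suspended.

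**Formula.** Let δ be the maneuver's effect in tolerant patients.

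- Arm difference over all randomized patients: δ + *p*Δ.
- Complete-case estimate: δ, in expectation.
- Imputation from T1 and arm: also δ, because missing patients receive the value expected for observed patients of their arm.
- Understatement: *p*Δ.

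Numbers in: 0.10 × 1 = 0.1; 0.10 × 2 = 0.2; 0.20 × 1 = 0.2; 0.20 × 2 = 0.4 SD.

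**Check by simulation.** 30 per arm, T1–T2 correlation 0.6 (assumed), 20 imputations from T1 and arm, estimates combined by Rubin's rules. All values are in SD of T2.

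| *p* | Δ | δ | All patients | Complete cases | Imputed | Understated by |
|---|---|---|---|---|---|---|
| 10% | 1.5 | 0 | 0.157 | 0.007 | 0.008 | 0.149 |
| 10% | 2 | 0 | 0.208 | 0.008 | 0.008 | 0.200 |
| 20% | 1.5 | 0 | 0.297 | −0.004 | −0.004 | 0.301 |
| 20% | 2 | 0 | 0.407 | 0.008 | 0.007 | 0.400 |
| 10% | 1.5 | 0.4 | 0.554 | 0.403 | 0.404 | 0.150 |
| 20% | 2 | 0.4 | 0.809 | 0.410 | 0.408 | 0.401 |

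The last column is the all-patients value minus the imputed value, and it matches *p*Δ. Complete-case and imputed estimates agree to within 0.002 SD in every row, so their agreement says nothing about the bias. With δ = 0.4 the suspended patients were imputed with a mean change of about 0.40, the change seen in their arm.

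**What it could do to the conclusion (illustration only).** Assume a margin of 0.5 SD, a T1–T2 correlation of 0.7, δ = 0 and two one-sided 5% tests on the T1-adjusted arm difference. With 3 patients suspended at 1 SD, the chance of declaring equivalence rises from 59% on full data to roughly two thirds on observed data. With 6 patients at 2 SD it rises from 6% to about 61%.

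**The case against.** The strongest reply is that the size comes from assumptions. The suspension rate, shift, correlation and margin are not in the article, and nothing there shows that a patient who reaches an airway-pressure or vital-sign limit has a higher P2/P1 at T2. That stands: the figures show what the plan could miss, not what will happen. The mechanism is still plausible on the article's own terms. The Introduction says that hyperinflation raises intrathoracic pressure and can influence intracranial pressure, and neurological instability is itself a reason to suspend.

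A second reply is that the imputation model is not stated and may sit in an analysis plan. The trial records vital signs, airway pressures and end-tidal CO₂, and adherence or withdrawal is to be a covariate. Good predictors would reduce the bias. They cannot be relied on to remove it: if suspended patients have no T2 reading, the data cannot show how their T2 differs, and recorded predictors help only by extrapolation. The choice of this method as the sole check is made in the article itself.

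Three stronger readings are tempting but unsupported:

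- *That the named tests cannot be pooled after imputation.* ANOVA contrasts have standard errors and pool by Rubin's rules. Rank tests can be pooled through their z values, and the simulation obtained a pooled Wilcoxon z in every scenario. An unprinted pooling rule is detail that an article may leave out.
- *That lost readings are filled in as no change.* They follow observed patients of the same arm, which equals no change only if those patients do not change.
- *That every interruption or suspension loses T2.* Interrupting the maneuver restores the ventilator settings and does not end measurement. Suspended collection need not stay suspended: *Interventions*, for the waiting period, has it start again later. The suspension rule also covers both arms.

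**Conclusion.** The point holds in a limited form. The only stated check shares the main analysis's reliance on observed patients, while the protocol's own rules make harm-related loss of T2 possible and more likely in the experimental arm. If such loss occurs, both analyses can lean towards the hoped-for conclusion without disagreeing.

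The understatement is the share suspended times their excess at T2: about 0.1 to 0.4 SD for 10% to 20% suspended and an excess of 1 to 2 SD. It is zero if no T2 reading is lost, and smaller if the imputation model uses informative predictors or if controls are suspended too. The lean towards equivalence also presumes that suspended patients do worse and that tolerant patients show little change or a worsening. The documents do not establish that the bias will occur or how large it would be. This is an inexpensive improvement to the sensitivity analysis; it does not invalidate the design.

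**What to change.** Keep multiple imputation and restate the sensitivity analysis as follows.

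1. Apply it to one estimate, the arm difference in P2/P1 at T2 adjusted for T1, combined across imputed data sets into a single estimate with a confidence interval.
2. Include recorded vital signs, airway pressures and earlier readings as predictors in the imputation model.
3. Add a delta-adjusted (tipping-point) scenario: for patients whose maneuver was interrupted or whose collection was suspended, shift the imputed T2 value upward in steps and report the shift at which the conclusion changes.
4. Report, per arm, how many patients were interrupted or suspended and how many T2 readings are missing.

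The cost is a few sentences in the analysis plan and a little extra analysis, with no new patients or measurements beyond a count of these events by arm. The downside is that the sensitivity result may be less favourable to equivalence.
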